#### Preparation, Planning, and Process Identification

The process map exercise described in this protocol is guided by the need to characterize common critical decision points that adequately represent the global DCM health care pathway. To obtain broad insights, we define the starting point as the time when a person with DCM is diagnosed with DCM and the end point as the time when a person with DCM engages in posttreatment management of the condition. We will define the patient group under investigation as people with moderate or severe DCM treated surgically and people with mild DCM treated nonoperatively [2]. This approach will ensure an all-encompassing investigation of the care route for people with DCM.

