#### Recruitment Strategy and Skills Training

Key informants—English-speaking adults (aged ≥18 years)—will be drawn from the specialized RECODE-DCM community using a convenience sampling approach. Professionals will be approached for participation if they belong to key clinical disciplines, including spinal surgery, neurology, combined physical and psychological rehabilitation medicine, physiotherapy, pain management, and primary care [4,108], and have at least 5 years of experience in managing DCM. People with DCM will be eligible if they have undergone surgical decompressive treatment at least 6 months before, the time point at which neurological recovery is considered to halt [107], and if they have experienced the common care pathway for spinal disorders from primary care to rehabilitative services [145]. This criterion will ensure that participants with DCM are familiar with a wide range of interventions and services along the global spinal care pathway and, therefore, can provide an informed view of its workflow and cognitive decision points. To ensure a global representation of the spinal care workflows and cognitive decisions, both professionals and participants with DCM will be sought at the previously described geographical target ratio. In addition, a 1:1 ratio corresponding to HCPs to people with DCM will be sought in the development of the baseline process map.

An electronic study pack will be provided to those interested in participating, comprising a written study summary, this study protocol, and a Participant Information Sheet containing the study investigators’ contact details. To equip respondents with the necessary process map skills, all consenting participants will be issued a short explanatory document outlining relevant process map symbols alongside an example of a finalized map from a different health care process. Participants will be given the opportunity to contact the study team should they have any questions or require further clarification before commencing study activities.

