#### Data Gathering

To enhance accessibility and foster participant engagement [146], data will be collected using one-to-one semistructured interviews, estimated at approximately 60 minutes and conducted via Google Meet. The interview schedules will be grounded in the literature, aiming to capture information on each step of routine clinical care under investigation [144,145]. To enhance comprehensiveness and incorporate expert input, the topic guide will undergo review and approval by the aforementioned steering group. In total, 2 distinct interview guides will be developed to interview clinicians and people with DCM. For clinicians, we propose a tailored approach in recognition of the specialization inherent in each HCP’s role. For example, primary care physicians are instrumental in recognizing the condition and its associated clinical examinations for referral to a spinal surgeon [42]. Specialist surgeons, under the remit of neurosurgery or orthopedics, play a pivotal role in steering the course of management [147]. Specialist practitioners such as physiotherapists play a vital role in assisting in the management of DCM via preoperative physiotherapy and neurorehabilitation programs, primarily used in the context of DCM to manage disability postoperatively [40,148]. Therefore, our interview guide will account for differences in specialists’ knowledge of care for DCM by asking HCPs an open question regarding how they manage people with DCM in their role specifically. From there, prompts relevant to each clinician’s profession and based on the information they provide will be used to guide the interview. By grounding the topic schedule in the particularities of each professional’s role, our approach can help ensure a thorough exploration of clinicians’ perspectives, accounting for the nuanced differences across specialties and individual clinical roles within the DCM care pathway. We also recognize that the care pathways of people with DCM differ owing to variations in patients’ DCM, flow times between different regions in the world, and guidelines of care [149]. Therefore, patients will be encouraged to share their experiences navigating the care system, focusing particularly on key decision-making points. Prompts will be used to elicit detailed accounts of their journey, the information sources they relied on, their understanding of their condition at each stage, and their level of satisfaction with the decision-making process. Interviews will be conducted until data saturation is reached, that is, until no new information is identified with respect to the research question [150]. At a minimum, it is envisaged that this will involve 20 interviews with HCPs and people with DCM. To allow for the incorporation of new insights generated during the data collection process, the interview guide may be adapted as necessary [151].

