In addition, we anticipate that the benefits of the process map in the international DCM care pathways may extend beyond SDM, for example, to addressing timely treatment and improving knowledge exchange [69]. Characterizing the key decision points and matching them to the current evidence base may expose critical knowledge gaps that must be served with targeted research. This means that, as the evidence is updated, so can be the SDM tool, helping accelerate the adoption of evidence into practice. In addition, providing a tangible visual tool to convey the patient experience across different health care settings and among various stakeholders may enhance communication among multidisciplinary teams [69], a recognized objective in DCM [172]. In the long run, the process map can serve as a valuable tool for patient advocacy, spotlighting areas of the care process that are particularly challenging [45], allowing policy makers and care providers to be better informed about the realities of living with DCM. This takes on added significance in low- and middle-income countries [173], where the burden of DCM is high yet access to care remains substandard [149]. Finally, developing a globally shared understanding of DCM care, with its similarities and differences, may facilitate opportunities for local redesign, development, or evaluation [69], leading to improvements in access to treatment [13].

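### Every patient interviewed for the process map must have reached rehabilitative services, so post-diagnosis decisions that ended without them have no direct patient account

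*Protocol article*

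**What the plan says.** Recruitment Strategy and Skills Training sets two joint conditions for patients. The first is surgical: "People with DCM will be eligible if they have undergone surgical decompressive treatment at least 6 months before". The second concerns the pathway: "if they have experienced the common care pathway for spinal disorders from primary care to rehabilitative services". The reason given is breadth of experience: "This criterion will ensure that participants with DCM are familiar with a wide range of interventions and services along the global spinal care pathway".

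The scope is set elsewhere. The Overview of Objective 2 defines a critical decision point as a juncture at which a discussion between professional and patient leads to a care decision, and calls these go-or-no-go decisions. Preparation, Planning, and Process Identification starts the map at diagnosis, ends it in posttreatment management, and defines the patient group as "people with moderate or severe DCM treated surgically and people with mild DCM treated nonoperatively". It adds: "This approach will ensure an all-encompassing investigation of the care route for people with DCM". Data Gathering accepts that pathways are not uniform: "We also recognize that the care pathways of people with DCM differ owing to variations in patients’ DCM", and also because of regional flow times and care guidelines.

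**The concern.** A go-or-no-go decision has two branches. An informant who must have reached rehabilitative services has, at that step, ended on the go branch. Patients who discussed rehabilitation and declined it, or for whom the discussion ended without onward referral, are excluded by rule. The map may therefore show the step into rehabilitation as a passage rather than a choice, or describe the no-go branch only as clinicians see it.

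This matters because the map is to guide which shared decision-making tools are developed, and a decision seen from one branch is a weak basis for a tool that supports both. Significance of the Study also hopes that the map can eventually serve patient advocacy by "spotlighting areas of the care process that are particularly challenging", with added weight in low- and middle-income countries, "where the burden of DCM is high yet access to care remains substandard". Where access is incomplete, the rule admits only patients whose access extended to rehabilitation.

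**Working it through.** The document states no figure on this point, and no hypothesis test or power calculation lies behind it. The check compares passages, with simple counts.

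**1. Is the criterion binding?** Yes. The two conditions are joined by *and*, and no later section admits patients who stopped earlier. Strengths and Limitations concedes in general terms that the sampling may not reflect all contexts, but does not mention this selection.

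**2. How many informants does it cover?** Data Gathering takes 3 patients and 3 surgeons from each target area, and Expert Selection names three areas.
- Baseline patients: 3 × 3 = 9
- Baseline surgeons: 3 × 3 = 9
- Baseline total: 9 + 9 = 18

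All 9 baseline patients, and every later patient, must meet the criterion.

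**3. How much later interviewing is assured?** Data Gathering envisages a minimum of 20 interviews with professionals and patients, and the wording allows two readings.
- 20 in total: 20 − 18 = 2 further interviews, with the split between professionals and patients not fixed.
- 20 per group: 20 − 9 = 11 further patient interviews.

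Interviewing continues to saturation, so these are lower bounds.

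**4. Could later steps recover the missing branch?**
- Saturation means no new information from those interviewed. It cannot reveal a branch that eligibility shuts out.
- Each participant checks a transcript and map, and final maps go back to participating stakeholders (Data Analysis). On the patient side, these are the same selected people.
- Professionals have no whole-pathway requirement and can report exits, but second-hand. In the baseline map the professionals are surgeons only.

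**5. Would dropping the criterion be enough?** The share q of otherwise eligible patients who did not reach rehabilitative services is not given. Purely as an illustration, take q as 10%, 20% or 30% with independent draws. The chance that n patients include at least one such person is 1 − (1 − q)^n.

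| n patients | q = 10% | q = 20% | q = 30% |
|---|---|---|---|
| 2 (20 in total, both further interviews with patients) | 19% | 36% | 51% |
| 9 (size of the baseline patient group) | 61% | 87% | 96% |
| 11 (20 per group) | 69% | 91% | 98% |

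Under the present rule every entry is 0. Without it, a group of 9 or 11 would probably include such a patient, but 2 further interviews might well not. These figures concern one such patient overall, not one per region. The remedy therefore needs deliberate recruitment as well as a wider rule.

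**6. Does the same sentence conflict with the defined patient group?** Yes, separately. The surgery condition excludes the nonoperatively treated people whom Preparation, Planning, and Process Identification places in the group. Removing that conflict would not remove the pathway restriction.

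**The case against.** The choice is deliberate and explained. In a study that may stop near 20 interviews, informants who have seen many services give more per interview. Other sources exist: professionals from several disciplines, including primary care and rehabilitation, are asked openly how they manage patients; other professionals join after the baseline map; pathway documents are used where possible; several maps may be drawn; and the supervising committee includes three people with the condition. How strict the common pathway is depends on a cited source that is not at hand.

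Much of this stands, and it rules out several stronger readings that a reader might infer:
- *The rule selects people for whom care worked.* Not supported. Reaching rehabilitation shows access, not a good result. The Introduction says most people have lasting disability despite treatment, and patients are prompted about their journey and their satisfaction with decisions. They can report delay, initial refusal and poor decisions.
- *Exit points are hidden.* Too strong. Professionals and documents can describe them.
- *Anyone who entered without primary care is a loss to the map.* The map starts at diagnosis, so routes before it are out of scope.
- *Every failure to be referred is a missed decision point.* By the document's definition a discussion must lead to a decision. Silent non-referral may not qualify; declining, or a discussion that ends without referral, does.
- *The bias is worst in Africa and Asia.* Expert Selection attributes difficulty there to research capacity and thin community membership. The remark on access concerns low- and middle-income countries, and the two are not equated.

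The objection does not answer the central point. The protocol accepts clinicians who know only their own stage and combines their accounts. The same logic allows patients to contribute collectively, so breadth does not have to be required of each one.

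**Conclusion.** The point holds in a limited form. By rule, all patient informants have experienced the pathway through to rehabilitative services, so post-diagnosis decisions that ended without those services have no direct patient account. This conflicts with the go-or-no-go definition, the claimed all-encompassing scope and the recognition that pathways differ.

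Its reach is certain: every patient interviewed, including all 9 in the baseline map. Its effect on content is not quantifiable, because the share of patients who do not reach rehabilitation is not given. The conclusion assumes that the criterion is applied as written and that experience through to rehabilitative services means having reached them. It affects the completeness of the secondary output, not the core information set. It should be corrected, but it does not invalidate the mapping exercise.

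**What to change.** - Keep the full-pathway criterion for the 9 baseline-map patients, which preserves the stated reason for it.
- Drop it for the later iterative patient interviews, and purposively seek in each region some patients who did not reach rehabilitative services.
- Reconcile the surgery condition in the same sentence with the patient group in Preparation, Planning, and Process Identification.
- If such patients cannot be recruited, state in the report that the map's exit points rest on professional accounts and pathway documents.

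The edit itself is a change of eligibility and recruitment wording. Some informants will cover fewer stages. Recruitment may be harder in regions thinly represented in the community, and because interviewing runs to saturation, the total may rise. If the minimum of 20 means all interviews together, the 2 beyond the baseline cannot supply one such patient in each of three regions, so a few more should be planned.

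A minimal alternative is to leave the criterion unchanged and declare the restriction under Strengths and Limitations. That costs nothing but leaves the gap in place.

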#### Data Gathering

To enhance accessibility and foster participant engagement [146], data will be collected using one-to-one semistructured interviews, estimated at approximately 60 minutes and conducted via Google Meet. The interview schedules will be grounded in the literature, aiming to capture information on each step of routine clinical care under investigation [144,145]. To enhance comprehensiveness and incorporate expert input, the topic guide will undergo review and approval by the aforementioned steering group. In total, 2 distinct interview guides will be developed to interview clinicians and people with DCM. For clinicians, we propose a tailored approach in recognition of the specialization inherent in each HCP’s role. For example, primary care physicians are instrumental in recognizing the condition and its associated clinical examinations for referral to a spinal surgeon [42]. Specialist surgeons, under the remit of neurosurgery or orthopedics, play a pivotal role in steering the course of management [147]. Specialist practitioners such as physiotherapists play a vital role in assisting in the management of DCM via preoperative physiotherapy and neurorehabilitation programs, primarily used in the context of DCM to manage disability postoperatively [40,148]. Therefore, our interview guide will account for differences in specialists’ knowledge of care for DCM by asking HCPs an open question regarding how they manage people with DCM in their role specifically. From there, prompts relevant to each clinician’s profession and based on the information they provide will be used to guide the interview. By grounding the topic schedule in the particularities of each professional’s role, our approach can help ensure a thorough exploration of clinicians’ perspectives, accounting for the nuanced differences across specialties and individual clinical roles within the DCM care pathway. We also recognize that the care pathways of people with DCM differ owing to variations in patients’ DCM, flow times between different regions in the world, and guidelines of care [149]. Therefore, patients will be encouraged to share their experiences navigating the care system, focusing particularly on key decision-making points. Prompts will be used to elicit detailed accounts of their journey, the information sources they relied on, their understanding of their condition at each stage, and their level of satisfaction with the decision-making process. Interviews will be conducted until data saturation is reached, that is, until no new information is identified with respect to the research question [150]. At a minimum, it is envisaged that this will involve 20 interviews with HCPs and people with DCM. To allow for the incorporation of new insights generated during the data collection process, the interview guide may be adapted as necessary [151].

A baseline map will be developed by interviewing 3 surgeons and 3 people with DCM from each of the geographical target areas. This approach seeks to ensure that international perspectives are adequately represented from the onset. As surgical intervention is the cornerstone treatment for DCM and surgeons preponderate the research community [50], professional transcripts derived from surgeons specifically (rather than other HCPs) will inform the preliminary map. As women remain underrepresented in clinical surgical practice [152], we will seek to recruit the views of at least one female spinal or orthopedic surgeon in the development of the baseline map. This preliminary map will be developed iteratively through a series of additional interviews with surgeons, other HCPs, and people with DCM while ensuring geographical representation. Interviews will be audio recorded and written informed consent will be sought from all participants. Following their interview, each participant will be provided with a copy of their transcript, a process map created from their interview data, and the evolving baseline map. Participants will be asked to reflect on their interviews and consider whether they wish to supplement the process map. This approach will be used as a means of ensuring data validation and quality and promoting further unbiased contributions to the data [153,154].

Upon reaching data saturation, a selection of interviews will be chosen based on their richness, and the final process maps will be refined by referring to them. Data richness will be defined as “thick” data that best capture the multifaceted complexities of the process under investigation [155]. Participants will be assigned unique study numbers to anonymize their identities in the transcripts.

#### Map Generation

The baseline map will be developed and schematically represented using Lucidchart (Lucid Software Inc), a web-based diagramming application, and developed iteratively based on information obtained during subsequent interviews. A level of complexity associated with ad hoc variation in the international processes and cognitive decision points is anticipated. To accurately depict this, several process maps may need to be generated. For example, a separate process map may need to be created for preoperative, operative, and postoperative processes. Where possible, relevant clinical pathway documents provided by participants will be used in the development of the process map.

#### Data Analysis

Interviews will be transcribed verbatim and analyzed using inductive thematic analysis according to Braun and Clarke [156]. This will involve a coding process whereby segments of text are systematically organized according to common concepts and broader themes developed to encapsulate the main topics present in the interview data. The synthesis of these themes will be used to develop a visual representation of the interview data within the process map. The map will be developed iteratively, ensuring the inclusion of emerging themes. The final stage will involve validation to ensure the accuracy and reliability of the process map. This can be achieved through methods such as member checking, peer debriefing, or triangulation, ensuring the credibility and dependability of the findings [157]. The final process maps will be shared with the key participating stakeholders for comments and validation over email. Participant demographic characteristics will be collected during the interviews and presented in tabular form using frequencies, means, and SDs as appropriate. For HCPs, demographic data will include age, gender, job title, a brief description of their duties, and number of years managing DCM. For people with DCM, this will include age, gender, occupation, year of diagnosis, and treatment (where applicable).

#### Future Steps

Process maps should be used to guide process improvement initiatives [158]. The process maps generated following this study protocol will inform future efforts by Myelopathy.org to develop SDM tools that will help people with DCM participate in making specific and deliberate choices regarding their health. In particular, at the time of writing this protocol, it is considered that identifying critical decision-making points will allow for the development of widely used evidence-based SDM tools such as patient decision aids [159-162] or patient road maps [28].

